### Qualitative study

#### Design and setting

The research project also comprises a qualitative interview study in the complete sample of practices, which was recruited for the quantitative study. The interviews with representatives in all practices aim to contextualize the role of network-related mechanisms of coordination in a broader range of influences. A purposeful subsample of low and high performing practices will be examined to explore hypotheses on network-related mechanisms. Focus group interviews with stakeholders and experts will be done to explore options for strategies that relate to cooperation networks.

First, representatives (usually a GP) of all 40 participating practices will be interviewed. Second, a purposeful sample of other individuals from these practices will be examined in more detail. Maximum variation will be sought by targeting 4 practices with high scores for coordination and implementation of recommended practices and 4 practices with low scores on these measures. In each of these practices, we aim to interview face-to-face or via telephone (depending on the interviewees’ preferences) three patients, a primary care provider, and another healthcare provider (e.g. physician or physician’s assistant). The targeted sample size for this study is therefore 40. Finally, an independent purposeful sample of 10 to 15 stakeholders in the German healthcare system and experts in healthcare innovation will be interviewed and involved in the interpretation of study findings.

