**Methods:**

Two related studies are planned: a) an observational study of healthcare provider networks, involving 600 patients with chronic (atherosclerosis-related) cardiovascular disease from 40 general practices and up to 320 healthcare providers (general practitioners, medical specialist, physicians’ assistants), and b) a qualitative interview study with up to 80 healthcare professionals and patients. Furthermore, we will analyse claims data of a large German health insurer to explore provider networks in ambulatory cardiac care.

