#### Study population and sampling

From publicly available lists of the Statutory Health Insurance Agencies of Baden-Württemberg (KVBW), Rhineland-Palatinate (KVRLP) and Saarland (KV Saarland), primary care practices within designated administrative districts will be randomly drawn and invited to take part in the study until the target sample size has been reached.

To enhance the homogeneity of the study population, we will focus on patients with coronary heart disease (as indicator for atherosclerotic vascular disease) and at least one other chronic disease (chronic heart failure, diabetes mellitus, chronic obstructive pulmonary disease, chronic renal failure or depression). Within these conditions, we will select patients with moderate to high disease severity, using ICD-codes. Primary care practices will be asked to invite 15 patients for the study. Primary care physicians, respectively their assistants, will be asked to generate a list of patients potentially eligible for our study by using their practice’s documentation software. Patients need to have visited the practice within the past 3 months; patients with a short life expectancy or major cognitive limitations will not be approached. The practice generates a printed list and removes potential identifiers except ICD-codes. Afterwards, one member of the research team visits the practice and randomly chooses the desired number of patients from the list. Alternatively, instructions for randomized sample drawing are sent to the practice and staff members choose patients accordingly themselves. The practice is then provided with a sufficient number of blank envelopes and questionnaires through the research team and will send out questionnaires to the selected patients. The patient receives the questionnaire, is free to fill it out and send it back anonymously directly to the research institute. The study was powered to detect a small to medium effect size (*r* = 0.15) on the primary outcome. Power was set at 0.8, significance level at 0.05, and a design effect of 1.4 (40 clusters and an intraclass correlation coefficient of 0.01) was taken into account.

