#### Primary and secondary outcomes

The primary outcome is patient-reported coordination of healthcare. Coordination of patient care is a multidimensional concept, often measured in terms of patient reported healthcare received [12]. For this study, a validated patient questionnaire will be applied: the Nijmegen Continuity Questionnaire, a 28-item questionnaire that covers personal coordination of care as well as multi-professional cooperation [13]. The measure has been applied and validated in primary care as well as ambulatory medical specialist care. It has been translated into German, using a forward and backward translation procedure, and pilot tested in a separate sample of patients before the main study began. The 4 items concerning inpatient care will not be used.

The main measures in this study map out the cooperation networks of healthcare providers.

The patient questionnaire will contain questions on healthcare providers involved and their cooperation up to 1 year before measurement. This method was successfully applied in previous research of the principal investigator [11]. The focus of the questionnaire will be on ambulatory cardiac care (primary care physician, physicians’ assistants, cardiologist). Based on previous research of the principal investigator [14], we refrain from measuring networks from the patient relatives’ perspectives.

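### The high and low performing labels for the eight interview practices rest on practice scores that, on the plan's own inputs, are mostly sampling noise, so single practices will often be mislabelled

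*Protocol article*

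**What the plan says.** The Protocol article (Qualitative study, Design and setting) seeks maximum variation by "targeting 4 practices with high scores for coordination and implementation of recommended practices and 4 practices with low scores on these measures". It states the purpose as follows: "A purposeful subsample of low and high performing practices will be examined to explore hypotheses on network-related mechanisms". Five interviews are planned in each of the eight practices, 40 in all. Under Study population and sampling of the same study, the subsample is recruited once the coordination and implementation scores have been calculated.

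The scores come from the patient survey. "Primary care practices will be asked to invite 15 patients for the study", which agrees with the Abstract's total: "involving 600 patients with chronic (atherosclerosis-related) cardiovascular disease from 40 general practices". For the primary outcome ("The primary outcome is patient-reported coordination of healthcare"), the sample size paragraph says that "a design effect of 1.4 (40 clusters and an intraclass correlation coefficient of 0.01) was taken into account".

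The article does not discuss how reliably 15 questionnaires measure a practice. It does not show how the two scores are combined for selection, and it gives no ICC for implementation of recommended practices.

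**The concern.** The performance labels are statements about practices, but the sample size paragraph assumes that only 1% of the variance in the coordination score lies between practices. With 15 patients or fewer behind each mean, an extreme score is then largely a matter of which patients were drawn and replied. A practice labelled high may be average or worse.

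What is at stake is interpretation. The interviews from these practices are to explore network mechanisms, and the qualitative Data-analysis section plans to link them with the quantitative results in joint displays. If the labels are taken at face value, features heard in a high practice may be read as reasons for good coordination in a practice that does not have it.

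**Working it through.** **Inputs.** ICC 0.01, design effect 1.4 and 40 practices (Quantitative survey study, Study population and sampling); 15 patients invited per practice (same section; 600/40 = 15); four high and four low practices (Qualitative study, Design and setting).

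**1. The plan's own figure.** Design effect = 1 + (m − 1) × ICC, where m is the number of patients per practice.
- m = 15, ICC = 0.01: 1 + 14 × 0.01 = 1.14. The stated 1.4 is not reproduced.
- Using the 40 clusters as the cluster size: 1 + 39 × 0.01 = 1.39, close to 1.4. This may be how it arose.
- Keeping 1.4 and m = 15: ICC = 0.4/14 = 0.029.

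The printed inputs therefore support two ICCs, 0.01 and 0.029. Both are carried forward.

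**2. Reliability of a practice mean.** Reliability = m × ICC / [1 + (m − 1) × ICC]; noise share = 1 − reliability.
- ICC 0.01, m = 15: 0.15/1.14 = 0.132; noise 87%.
- ICC 0.029, m = 15: 0.429/1.40 = 0.306; noise 69%.

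Fifteen is the number invited. The article gives no response rate, so fewer returns are an assumption. At ICC 0.01, 12 returns give 89% noise and 9 returns give 92%. At ICC 0.029, 9 returns give 79%.

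**3. What selection at the extremes would yield.** Simulation of 40 practices with normal practice effects and normal patient error, taking the top four and bottom four by observed mean coordination score. The article does not state this exact rule; it is the simplest reading, on one of the two scores. Gaps are in patient SD.

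| | ICC 0.01, 15 returns | ICC 0.029, 15 returns | ICC 0.01, 9 returns (assumed) | ICC 0.029, 9 returns (assumed) |
|---|---|---|---|---|
| Observed gap, high minus low | 0.93 | 1.03 | 1.17 | 1.25 |
| True gap | 0.12 | 0.32 | 0.10 | 0.26 |
| True gap if selection were perfect | 0.34 | 0.57 | 0.34 | 0.57 |
| High practices truly in the top four | 24% | 35% | 21% | 29% |
| High practices truly below the median | 26% | 14% | 31% | 20% |
| A high practice truly below a low one (pairs) | 18% | 6% | 24% | 11–12% |
| Group means in the right order | 97% | over 99% | 92% | 99% |

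Check: true gap = reliability × observed gap, so 0.132 × 0.93 = 0.12 and 0.306 × 1.03 = 0.32.

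**4. Sensitivity to the ICC.** If the ICC were 0.05 or 0.10 (assumed), noise at 15 returns would be 56% or 38%, and 8% or 3% of high practices would truly be below the median.

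**The case against.** The strongest reply is that this is purposeful sampling for exploratory interviews. No statistical test rests on the eight practices, and representatives of all 40 practices are interviewed. Patients in the subsample are newly drawn, and codes stay linked to individual cases. All of this stands, and it limits the harm. It does not repair the labels: sampling on an attribute still presumes that the cases have it, and the article names the groups by performance.

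A second reply is that an ICC used for a power calculation is a planning assumption, not a measured variance. That also stands. It is the reason to estimate reliability from the survey data before the labels are used.

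A reader might infer more from the figures than they support:
- *That the rule cannot produce a contrast, or that the groups hardly differ.* At ICC 0.01 the group means are in the right order in about 97% of replicates and differ by 1.2 between-practice SD. The patient-scale gap is small partly because an ICC of 0.01 itself says practices differ little; even perfect selection would give only 0.34 SD.
- *That the whole selection is 87% noise.* The figure covers the coordination score at one of two ICCs. Selection also uses the implementation score, whose ICC is not given and which may be more reliable or less.
- *That any mechanism found would merely explain noise.* The article does not set out a high-versus-low comparison as the basis for inferring mechanisms.

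**Conclusion.** The concern holds for the labels of single practices, not for the existence of a contrast. On the plan's inputs, 69% to 87% of the variance in practice coordination means is sampling noise, and more with non-response. With selection at the extremes of that score, about one in seven to one in four high practices would truly be below the median, and the observed gap would be roughly three to eight times the true one (1.03/0.32 to 0.93/0.12).

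This rests on all 15 invited patients replying, normal distributions, selection on the coordination score alone, and an ICC of 0.01 or 0.029. A true ICC near 0.10 would largely remove the problem. The article gives no basis for expecting one, and its ICC and design effect need to be reconciled in any case.

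**What to change.** 1. Before choosing the eight practices, estimate the between-practice variance and the reliability of practice means for both scores. The random coefficient models planned in Phase 4, Step 2 supply this. For this purpose, fit them without the network predictors, which would absorb part of the between-practice variance.
2. Select on the model-based (shrunken) practice estimates rather than raw means. With equal returns this leaves the ranking unchanged; it matters when returns differ, because it stops practices with few replies from filling the extremes.
3. Fix a minimum reliability in advance and report the value obtained. For scale: a threshold of 0.6 with 15 returns needs an ICC of 0.6/(15 − 14 × 0.6) = 0.09.
4. If the threshold is met, the performance labels may stand. If not, describe the groups as practices with high or low observed scores, and do not interpret differences between them as explaining coordination performance.
5. Reconcile the ICC of 0.01 with the design effect of 1.4.

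Selecting on provider-reported network features instead is an option, not a required correction. It gives up contrast on the outcome, and the reliability of the network data has itself still to be examined (Phase 1).

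The cost is one small calculation and a more cautious claim. The eight practices and 40 interviews stay as planned.

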#### Study population and sampling

Representatives of primary care practices in the quantitative study phase will all be invited to participate in this interview study. Recruitment of the subsample will be carried out separately after completion of the necessary calculations regarding coordination and implementation. Here, physicians and practice staff of the selected practices will be invited to participate. Regarding patient interviews, new patients will be randomly selected and invited to take part.

#### Interviews

Interviews with representatives of practices will be semi-structured and cover a range of potential determinants of healthcare coordination, such as cultural factors, financial consequences, and patient expectations. This will help to interpret the role of network-related factors in relation to other determinants of healthcare coordination. Semi-structured interviews, organised by a pilot-tested interview guide and conducted by trained interviewers, will focus on network-related determinants of coordination. Besides exploration of the hypothesised mechanisms, the interviews will also contain open questions to identify further factors and mechanisms related to networks.

Focus group study. Based on earlier research of the principal investigator [19], we will organize focus groups (6–8 participants per group) led by trained facilitators to identify potential strategies that build on network-related factors to improve healthcare coordination. In the group meetings, key information from the research will be presented, followed by a brainstorm among participants.

All interviews will be audiotaped and fully transcribed by trained staff. Data will be kept confidential and pseudonymized in a secured place, with the key to personal identifiers in a separate place; personal identifiers will be destroyed after use.

#### Data-analysis

The qualitative study relates to research objective 2, which concerns network-related mechanisms of information exchange and collaborative work in the healthcare setting. The study aims to provide insight into patterns of context, mechanisms, and outcomes [20]. It will particularly explore which social network characteristics influence mechanisms of information exchange and collaborative work in healthcare delivery networks.

For organizing the steps in the data-analysis, we will apply the framework method, which is a structured, stepwise approach that centres around a matrix of cases (usually participants) in rows and interpretations (codes, categories, etc.) in columns [20]. In this way, codes and categories remain linked to cases. The framework method is not inherently deductive or inductive, and we will use both. In the deductive approach, we will use the conceptual framework for network-related factors of healthcare coordination, which was developed for this proposal (Fig. 1), and a comprehensive framework of 57 conceptual determinants of implementation of practices into healthcare practice, which has been systematically developed in previous research of the principal investigator and has proven to be useful in a range of studies [19].

**Fig. 1 Fig1:**
[figure not shown]
Conceptual model showing hypothesized mechanisms affecting coordination of care

Following published guidance [21], the following stages are planned: After interviews have been fully transcribed (stage 1), the researchers will familiarize themselves with the transcripts by reading these line-by-line (stage 2). Then relevant sections of the transcripts will be coded: descriptive or conceptual labels will be attached (stage 3). Following Emerson et al. [22], we will apply open coding first (coding anything that might be relevant from different perspectives). This is followed by focused coding in a fine-grained analysis on the basis of the concepts in the pre-defined frameworks. At least two researchers will be involved in the coding of the initial interviews. They will meet after coding initial interviews in order to develop a working analytical framework, in which codes have been organized in categories (clusters of codes) (stage 4). They will then code additional interviews and meet again; this will be repeated until the framework has been consolidated. The resulting framework will be applied to the remaining interviews (stage 5).

After completion, a spreadsheet is used to create a matrix in which the codes are charted in relation to participants (stage 6). Throughout the data-analysis, reflections on the interpretation of data will be documented in analytical memos and used to generate interpretations in discussion with researchers, patients and clinicians (stage 7). Finally, linkages between the findings of quantitative data-analysis and the results of the qualitative analysis will be explored, using available options for joint visual display of findings from mixed-methods research [23].

Combining two-step analytical coding in the framework analysis [20] facilitates accumulation of scientific knowledge, because it relates findings to available theories and helps to identify factors and mechanisms that are currently not well covered by theories. A team of trained qualitative researchers will conduct the different steps and cross-check the consistency of the thematic analysis and categorization within the iterative process. Software for qualitative data-analysis (MaxQDA) is applied for logistical support. Data saturation is considered reached when no more new aspects can be identified in the interviewees’ statements.

### Claims data study

#### Design and setting

As the third component of the research project, an independent study (not related to the questionnaires or interview) is planned, based on an anonymized set of administrative claims data. These data will be derived from AOK (“Allgemeine Ortskrankenkasse”) Baden-Württemberg, the largest health insurer in the state, covering about 45% of the 11 million inhabitants. By using claims data, real world data is used instead of questionnaire based data, and it allows to include far more participants and thus increase statistical power to be able to detect smaller effects on clinically relevant outcomes. This is especially important for social network analysis in which missing nodes can significantly affect the results. Moreover, a near to full sample from all physicians is achieved, even if only 45% of the population is included in the sample, adding to the generalizability of our study at large.

#### Study population and sampling

The study population will be adults with recorded coronary heart disease and adults with heart failure regardless of date of diagnosis. For practical purposes, the focus is on patients and health providers in Baden-Württemberg only. Patient-Provider contacts for healthcare delivery, whether by face-to-face, telephone or online (excluding contacts for administrative/logistic purposes only, e.g. making an appointment) will be counted (concentration of care with a single provider). Given the source of the data, only financially reimbursed visits, are covered. Also recorded will be all visits to ambulatory providers, including physicians, psychologists, therapists and hospitals. Pharmacies and diagnostic laboratories are excluded given their complementary role in health delivery. These records will be at least 2 years old upon receipt.

#### Measures

Following a previous empirical study, claims data are used to construct two indices to assess the coordination of healthcare: a) the concentration of care with a single provider and b) number of handoffs of information required between providers [24]. The previous study suggested that these records were highly correlated with measures of the degree of collaboration between different providers during an episode and degree of coordination required between different providers during an episode [24]. As a third outcome, we measure hospitalization for chronic cardiovascular disease patients as an indication for adverse effects of suboptimal treatment.

#### Data analysis

Data preparation and analyses using the claims data will be performed with the relational database MySQL and R. In the first phase, network characteristics will be calculated wherever possible. These include independent measures that theoretically could influence our outcomes and involve among others: network density and homogeneity, the existence of a central care provider, and change of network composition. As outcomes, we will calculate measures that assess coordination of healthcare: a) the Bice-Boxerman Continuity of Care Index (COC) [25] that indicates the concentration of care with a single provider and b) the Sequential Continuity Index (SECON) [26] that indicates the number of handoffs of information required between providers. Additionally, a more clinically relevant outcome will be included by calculating hospitalization.

In the second phase, we will explore whether the hypothesised network-related mechanisms relating to central care providers, network density, network homogeneity, and change of network composition are associated with measures of coordination of care and hospitalization rates. All analytic analyses will be adjusted for patient characteristics, such as age, sex, and prevalence of comorbidities.

## Discussion

This study aims to provide insight into factors, processes and mechanisms of information transfer and interprofessional collaboration, which affect seamless, evidence-based healthcare practice. The results will ultimately contribute to the design of strategies for improving health care practice and to the development of measures of coordination for future research.

There is an extensive body of research on the impact of social networks on human behaviours, including collaboration beyond immediate self-interest [7, 8]. Few of the insights emerging from this research are related to healthcare providers, and social network studies in healthcare providers tend to be largely descriptive [27]. The planned research project will essentially test a number of hypotheses, which were derived from the broader non-health literature, and simultaneously explore health-specific processes (such as the content of referral letters). We are uncertain to what extent healthcare professionals and patients recognize and report network-related processes. Previous studies suggested that the range of factors, mechanisms and processes is substantially broader than perceived and reported by patients or providers in interviews [28].

The findings of the study aim to contribute to the design and evaluation of future interventions, particularly programs for improving coordination and enhancing evidence-based practice. We expect that network-related factors can be used to tailor the main intervention according to these factors. For instance, different approaches may be required in regions with well-connected physicians than in regions with loosely connected physicians. It remains to be seen to what extent discrepancies exist between factors that are perceived to be relevant and factors that are found to influence relevant outcomes, but are not perceived as such.

Given the specific features of the German healthcare system, such as medical specialists in ambulatory care practices, it also remains to be seen to what the findings can be generalized to other healthcare systems (or even states within Germany). Beyond exploring the specific issues in one German state, the project aims to provide fundamental insight into healthcare coordination and the impact of networks that emerge from sharing patients on healthcare providers' professional behaviours.

